### **10.3 Medical History**

A study physician and/or study coordinator will review the following with the subject/parent or legal guardian:

- ☐ Current and past prescription medications and doses
- ☐ Current and past medical history
- ☐ Review of systems
- ☐ Family history

The subject's medical history will be reviewed at each study visit. This will include query of the subject and parent or legal guardian (as applicable) regarding any changes since the last study visit. If a participant has a greater than 2-week history of cough a CXR will be obtained to screen for active TB.

### **10.4 Laboratory Evaluations**

Blood and urine will be collected at the time points described in the Schedule of Events.

Complete blood count with differential (CBCD), liver function tests (LFTs), lipid panel, and basic metabolic panel (BMP) will be performed at Quest Diagnostics or LabCorp at Screening, Week -8, Day 1, Week +2, Week +4, Week +8, Week +12, Week +16, Week +20, Week +24 (only if dose increased at week +16), Week +36, and Week +44. Thyroid function tests (TSH, Free T4) and Quantiferon-TB Gold test will be obtained at Screening.

Anti-anakinra antibodies will not be measured during this pilot study; the rationale for this is based on prior studies showing no effect of anti-anakinra antibodies on pharmacokinetic (PK) parameters, efficacy outcomes or adverse events (AEs) and low incidence of neutralizing anti-anakinra antibodies. However, serum will be collected at Day 1, Week +8, Week +36, and Week +44 and stored for possible future testing of anti-anakinra antibodies if needed for interpretation of safety or efficacy results.

Plasma will be collected and stored for future PK studies at Day 1, Week +8, Week +36, and Week +44.

For post-menarche female patients, a urine pregnancy test will be performed at Screening and at each study visit.

Plasma, serum, urine, and PAXgene tube for RNA will be collected for future biomarker studies at Week -8, Day 1, Week +8, Week +16, Week +36, and Week +44. Consent will be requested to perform these additional biomarker studies on

stored samples in the future as well as genome wide association studies (GWAS) and/or large-scale genomics/transcriptomics assays such as sequencing, methylation and expression.

Buffy coat for DNA will be collected for future biomarker studies at Week -8, Day 1, and Week +36.

Stool will be collected at Week -8, Day 1, Week +8, Week +16, Week +36, and Week +44 for future microbiome studies.

Whole blood will be collected at Week -8, Day 1, Week +8, Week +16, Week +36 and Week +44.

### ***10.5 Physical examination and Anthropometrics***

A trained pediatric provider will perform a physical examination at each visit that will include a detailed lymph node assessment. Tanner staging of pubertal development, including breast and pubic hair development in girls, and testicular size and pubic hair development in boys will be performed each study visit.

Standard anthropometric measurements including standing height and weight will be performed. Height or supine length if unable to stand will be measured 3 times standing without shoes. The average of 3 measurements by the same observer using identical technique with a wall-mounted stadiometer will be recorded. Each subject will be repositioned between each measurement. Height standard deviation score (SDS) will be calculated based on the National Center for Health Statistics 2000 data as provided by the Center for Disease Control. Weight to be measured standing, once with subject in light clothing or dressing gown with shoes removed. Height and weight measurements will be used to calculate body mass index (BMI) as weight (kg) divided by height (m^2).

### ***10.6 Sleep***

Sleep will be assessed using two methods:

1. Sleep Diary – Parents will record daily for 1 week during Week -6 (to avoid the effects of travel on sleep) and then 1 week prior to each study visit after that, the following information:
  - Number of night time awakenings
  - Duration of nighttime awakenings

- Number of consecutive hours of sleep overnight
- Length of time to get child to sleep at bedtime (first of the night)
- Number of daytime naps
- Length of daytime naps

## 2. Child Sleep Health Questionnaire (CSHQ)

The CSHQ is a parent questionnaire that has been used in many studies to examine both behavioral based and medical based sleep problems in children. The CSHQ yields a total score and eight subscale scores: 1) Bedtime Resistance, 2) Sleep Onset Delay, 3) Sleep Duration, 4) Sleep Anxiety, 5) Night Wakings, 6) Parasomnias, 7) Sleep-Disordered Breathing, and 8) Daytime Sleepiness. It has been validated in multiple groups including community children, children with diagnosed sleep disorders, children with development delay, and children with autism .

### **10.7 Stooling**

Stooling will be measured using a newly developed stooling survey titled “Sanfilippo Stool Habit Questionnaire” which was designed based on PROMIS stooling surveys. The survey covers stool pattern (e.g. consistency, frequency, ease), stooling interference with daily activities, influence on behavior, stooling related medications, and dietary interventions.

### **10.8 Sanfilippo Behavior Rating Scale (SBRS)**

The SBRS is a 68 item questionnaire, developed by Shapiro et al to assess the behavioral phenotype of children with MPS III and its progression over time. There are 15 scales that rate orality, movement/activity, attention/self-control, emotional function including Anger and Fear, and Social Interaction. In addition, 12 scales are grouped into four abnormality clusters: Movement, Lack of Fear, Social/Emotional and Executive Dysfunction.

### **10.9 Non-communicating Children’s Pain Checklist-Revised (NCCPC-R)**

The NCCPC-R is a validated scale for measuring pain in children with severe cognitive impairments. It includes 7 scales that measure vocal, social, facial, activity, body and limbs, physiological, and eating/sleeping indicators of pain. A combined total score for pain is calculated as well.

### **10.10 NIH Patient Reported Outcomes Measurement Information System (PROMIS)**

Per PROMIS guidance, we selected the 10 most relevant questions for parents of children with MPS III from the PROMIS Parent Proxy Fatigue item bank to make a

customized PROMIS Fatigue - Parent Proxy Custom Short Form. Customized short forms are scored using this online scoring service:

[https://www.assessmentcenter.net/ac\\_scoringervice](https://www.assessmentcenter.net/ac_scoringervice)

### **10.11 Autism Parenting Stress Index (APSI)**

The APSI was developed following many interviews of parents of children with autism. The Items fall into three categories: the core social disability, difficult-to-manage

behaviors, and physical issues. The APSI measures how much stress related to these three categories the parents are experiencing. The overall APSI scale score has been validated for parents of children with autism and other developmental disabilities.

### **10.12 Seizures**

Seizure frequency, duration, and severity will be reported by the caregiver in real time in a study diary or by texting the research group (based on caregiver preference).

### **10.13 Disordered Movement**

The duration, severity, and type (e.g. dystonia, chorea) of movement abnormality will be reported by the caregiver in real time for 1 week at a time in a survey. Duration will be quantified as:

- ☐ Occasional (<25% of the time)
- ☐ Intermittent (25-50% of the time)
- ☐ Frequent (50-75% of the time)
- ☐ Constant (>75% of the time)

Severity will be quantified as:

- ☐ The movement has interfered more with my child's daily activities
- ☐ The movement has interfered less with my child's daily activities
- ☐ No change in the severity of the abnormal movement

Optional: The parents can take a short, representative video of the movement disorder on the days they are recording it as above.

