- Autism **Parenting Stress** Index (APSI): MCID = 0.25 SD for Stress Total 
  - Ability to communicate
  - Tantrums/meltdowns
  - Self-injurious behavior
  - Difficulty making transitions from one activity to another
  - Toilet training
  - Not feeling close to your child
  - Concern for your child not being accepted by others
  - Concern for the future for your child living independently
- PROMIS **Fatigue** - Parent Proxy Custom Short Form: MCID = 3-point change
- **Seizures** – Parents will record each seizure in a seizure journal provided by the study. Information recorded will include the duration (average length of seizure), and need for medical intervention (e.g. rescue medication, medical evaluation).

- **Movement** disorder (e.g. dystonia, chorea, etc.) – Parent reported duration and severity. Change in one of two characteristics for +/-1 score, +/-2 score for change in two of the characteristics.
- Non-communicating Children's **Pain** Checklist-Revised (NCCPC-R): MCID = 0.25 SD

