### Secondary Endpoints:

Within individual change over 8-week treatment period (on maximum effective and tolerated dose) compared to change over 8-week observational period, and from Day 0 to Week +36 (i.e. treatment phase) in:

1. Incidence of treatment-emergent adverse events and laboratory values over 36-weeks of treatment to known frequency of anakinra-related AEs in other populations.
2. MDRI comprised of:
  - Sanfilippo Behavior Rating Scale (SBRS): Minimal Clinically Important Difference (MCID) = 0.25 SD for each scale
  - Child Sleep Health Questionnaire (CSHQ): MCID = 1-point change 
  - Autism Parenting Stress Index (APSI): MCID = 0.25 SD for Stress Total 
  - PROMIS Fatigue - Parent Proxy Custom Short Form: MCID = 3-point change
  - Movement disorder (e.g. dystonia, chorea, etc.): Parent reported duration and severity. Change in one of two characteristics for +/-1 score, +/-2 score for change in two of the characteristics.
  - Non-communicating Children's Pain Checklist-Revised (NCCPC-R): MCID = 0.25 SD

The MDRI will be calculated as the sum of scores from the components. Subjects will receive a score for each component of the MDRI listed above. A score of 0 will be given for a change in score less than the MCID. A score of +1 (improvement) or -1 (worsening) will be given for a change in score of  $\geq 1$  MCID and  $< 2$  times MCID. A score of +2 (improvement) or -2 (worsening) will be given for a change in score of  $\geq 2$  and  $< 3$  times MCID. A score of +3 (improvement) or -3 (worsening) will be given for a change in score of  $\geq 3$  times MCID. Seizures and movement disorder outcomes will be scored as described above.

3. Individual Clinical Response (ICR) – 5 most impactful clinical problems reported by the caregiver. Sum using 5-point Likert scale for each ICR element.

4. Gait: Qualitative assessment by physical therapist (i.e. improved, no change, worsened).
5. Stair climb/descent: Time and quality of movement.
6. Sleep Diary (1-week recall): Sum of the number of overnight awakenings, average duration of overnight awakenings, and duration of time for initial sleep onset at bedtime.
7. Stooling Survey.

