| Sanfilippo Behavior Rating Scale                       |           | X                               | X                 |                                                              | X                                | X                                      |
| Non-communicating Children's Pain Checklist-Revised    |           | X                               | X                 |                                                              | X                                | X                                      |
| Parent reported outcomes (PROMIS) d         |           | X                               | X                 |                                                              | X                                | X                                      |
| Seizure - parent assessment x 1 week                   |           | X h                  | X                 |                                                              | X                                | X                                      |
| Movement - parent assessment x 1 week                  |           | X h                  | X                 |                                                              | X                                | X                                      |
| Individual Clinical Response                           |           | X                               | X                 |                                                              | X                                | X                                      |
| Gait assessment                                        |           | X                               | X                 |                                                              | X                                |                                        |
| Vineland-III                                           |           | X                               |                   |                                                              | X                                |                                        |
| Stair climb                                            |           | X                               | X                 |                                                              | X                                |                                        |

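### Movement severity is a more/less/no-change rating with no stated reference time, and no single reference gives all the severity changes the endpoints need

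*Protocol*

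**What the plan says.** Section 10.13 says that movement abnormality "will be reported by the caregiver in real time for 1 week at a time in a survey". It has two scored characteristics.

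- **Duration** is an absolute category with four levels, starting at "Occasional (<25% of the time".
- **Severity** has three possible answers: "The movement has interfered more with my child's daily activities", "The movement has interfered less with my child's daily activities" and "No change in the severity of the abnormal movement". No comparison time is given here, in 9.1, in the schedule and its footnotes, or in 27.7.

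Section 9.1 scores the component as follows: "Change in one of two characteristics for +/-1 score, +/-2 score for change in two of the characteristics". The same rule serves the Phase 2 primary endpoint, where movement is one of the symptoms parents may select, and the MDRI secondary endpoint.

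Change is needed over several intervals. The primary endpoint sets the 8-week treatment change against the 8-week observational change. The secondary endpoints add change "from Day 0 to Week +36 (i.e. treatment phase"). Section 27.7 looks at Day 1 to Week +8 and then at Week +8 to Week +16.

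The schedule row "Movement - parent assessment x 1 week" places surveys at the Week -8 column (completed at Week -6 by footnote), Day +1, and Weeks +8, +16, +36 and +44.

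**The concern.** A duration category is a level, so two surveys can be compared over any interval. A severity answer is already a change, and it covers only the interval the parent had in mind. Since the protocol does not fix that interval, the parent may be comparing with the previous survey, with Day 1, with study entry, or with the week before.

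Two results depend on it. One is the severity half of the movement component in the MDRI, above all for Day 0 to Week +36, where a maintained improvement could be recorded as no change. The other is the assessment of improvement or worsening at Weeks +8 and +16 for any child whose parents chose movement as a most bothersome symptom.

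An analysis plan could choose a reading, but it could not establish afterwards what comparison parents made, nor recover a severity level that was never recorded.

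**Working it through.** The protocol gives no figure for this item, so there is none to reproduce. The check takes each plausible reference time and asks whether each required interval can be scored. Coding: less = +1, no change = 0, more = -1. Patterns are counted, not weighted by how likely they are. Day 0 is taken as the Day 1 survey.

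| Interval needed | Source | Reference = previous survey | Reference = Day 1 |
|---|---|---|---|
| Observational period (Week -6 to Day 1) | 9.1 | Day 1 answer | not measured |
| Day 1 to Week +8 | 9.1, 27.7 | Week +8 answer | Week +8 answer |
| Week +8 to Week +16 | 9.1, 27.7 | Week +16 answer | unknown in 2 of 9 pairs |
| Day 0 to Week +36 | 9.1 | not determined | Week +36 answer |

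**Reference = previous survey.** Three answers span Day 0 to Week +36: at Week +8, Week +16 and Week +36. That gives 3 × 3 × 3 = 27 patterns.

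- Patterns with both a +1 and a -1: 27 - 8 (no +1) - 8 (no -1) + 1 (neither) = 12. The answers carry no step size, so the net direction cannot be recovered in these 12, even if all three answers are combined.
- The other 27 - 12 = 15 have a known net direction. Suppose the Week +36 answer alone is used. It reads 0 despite net change when the last answer is 0 and the first two are not both 0 and point the same way: (+1, 0), (0, +1), (+1, +1) and their mirror images, so 2 × 3 = 6 patterns. The sustained responder is one of these: (+1, 0, 0) has net direction +1 but a Week +36 answer of 0.
- If all steps are assumed equal in size, the Week +36 answer differs from the net direction in 12 of 27 patterns and has the opposite sign in 2: (less, less, more) and (more, more, less).

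**Reference = Day 1.** The Week +8 and Week +36 answers are the required changes. For Week +8 to Week +16 there are 3 × 3 = 9 answer pairs. Seven fix the direction; for example, less then no change is a worsening. Two do not: less/less and more/more. In less/less the child is better than at Day 1 on both occasions but may have gained further or slipped part of the way back. That matters here because the Week +16 rule concerns children who had improved by Week +8.

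**Size within the MDRI.** The secondary-endpoint list in 9.1 has six components. Movement scores up to 2 in either direction, from two characteristics, so severity carries 1 point in either direction. Duration still yields a change for every interval.

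**The case against.** The best defence is that the rule in 9.1 needs only a direction of change, and the severity item supplies one. With the previous survey as reference, the Day 1 answer is the observational change and the Week +8 answer is the treatment change, which are the two periods the primary endpoint compares. The Week +16 answer then gives the later change used in 27.7. No Week -6 baseline is needed. The survey form is not shown and may state a reference. All of this stands, and it confines the problem. It does not remove it: a reference printed on the form would settle which column of the table applies, but neither column is complete.

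Several stronger readings are tempting and do not hold.

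- A reader might infer that the movement score or the MDRI cannot be computed. Duration is absolute and always gives a change, and the adjacent-survey severity changes can be read under the previous-survey reference.
- A reader might subtract one severity answer from another and note that 4 of 9 Day 1/Week +8 pairs then give the wrong category. No section prescribes that subtraction, and none of the four reverses the sign of the Week +8 report.
- A reader might conclude that a sustained response is scored as no response. That concerns the severity point only, and only under the previous-survey reference.
- The limit of 2 on movement, against 3 for the other components, is a stated scoring choice and not part of this defect.
- Movement disorder is not a requirement for entry. Section 5.2 lists it as one of six criteria of which two suffice, with a separate alternative route.

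**Conclusion.** The point holds in a limited form. The severity item has no stated reference time, and neither of the two natural references gives every severity change that 9.1 and 27.7 call for. Under the previous-survey reference, the Day 0 to Week +36 severity change is undetermined in 12 of 27 patterns, and a held improvement loses its severity point if the Week +36 answer is used alone. Under the Day 1 reference, the observational change is missing and Week +8 to Week +16 is unknown in 2 of 9 pairs.

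The effect is confined to the severity point of one of six MDRI components, in children with a movement disorder, and to the Week +8 and Week +16 assessments where movement was chosen. The pattern counts show what the answers can and cannot identify; they are not error rates. The conclusion assumes that the protocol text describes the item as parents see it.

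**What to change.** Replace the severity item in 10.13 with an absolute ordinal rating of how much the movement interfered with daily activities over the recorded week, asked at every survey. In 9.1, state that change is the difference between the two surveys bounding each interval: Week -6 to Day 1, Day 1 to Week +8, Week +8 to Week +16, and Day 1 to Week +36.

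For surveys already collected, state what reference parents were given.

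- If it was the previous survey, use the severity answers directly for adjacent-survey intervals only. Score the Day 0 to Week +36 movement change on duration alone and report severity there descriptively.
- If the reference cannot be established, score duration alone throughout.

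The cost is one survey item and one sentence in 9.1, with no added visits. The drawback is that earlier severity answers cannot be converted to the new scale, so children already surveyed contribute less severity information.

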### **10.14 Individual Clinical Response (ICR)**

The 5 most important clinical problems will be determined by the caregiver. Examples will be offered based on previous work that include sleep disturbances, hyperactivity, frustration/impulse control/aggressive behaviors, feeding, anxiety, unhappiness, communication, social deficits, digestive issues and toileting, pain, illness/vulnerability to illness, fatigue, seizure, mobility, and gait. The caregiver will rate their top 5 outcomes on a 5-point Likert scale as follows:

0 - Not stressful

1 - Sometimes creates stress

- 2 - Often creates stress
- 3 - Very stressful on a daily basis
- 4 - So stressful sometimes we feel we can not cope

### **10.15 Gait Analysis**

Gait will be filmed from 3 directions while the participant walks 30 meters and total time to complete the 30 meters will be recorded. These films will be viewed and rated by a certified pediatric physical therapist. Videos will be stored on the secure LI server indefinitely.

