## 10.0 Procedures Involved

### 10.1 Study design

This is an open label, single center, pilot study of 20 participants with MPS. There will be an initial screening visit, followed by an 8-week observational period, then a

36-week treatment period, and finally another 8-week observational period to determine any effects of withdrawal from the treatment. Total duration of subject participation is 52 weeks.

[figure not shown]

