### **10.17 Stair Climb**

A 1-flight stair climb will be filmed and evaluated for ease of climb/descent (i.e. amount of assistance, redirection, etc.) and total time required to complete stair climb and descent. Videos will be stored on the secure LI server indefinitely.

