### **Secondary objective**

Outcome variables include Individual Clinical Response (ICR, 0~25: sum of the top 5 domains on a 5-point Likert scale), Gait analysis results (improved, no change, worsened), Stair climb/descent (time and quality of improvement), Sleep diary (sum of the number of overnight awakenings, average duration of overnight awakenings, and duration of time for initial sleep onset at bedtime), and Stooling survey results. For univariate analyses, similar statistical tests will be used as ones used for the primary objective, depending on the data type of the outcome for comparing two study periods. For multivariate analyses, mixed effect models (linear for continuous outcomes and non-linear such as multinomial logistic regression for categorical outcomes and Poisson (or Negative Binomial regression model, if over-dispersion is apparent) for count outcomes) will be used using 2-4 different time points (pre-observation, 8, 36 week treatment, post-observation periods) as within subject factor. Covariates such as sex and age will be considered in multivariate models if they are found to be statistically significant in changes of outcomes. Sub-scale analyses will be conducted if changes in the composite score are found to be statistically significant or are reached to a clinically meaningful boundary. We expect to have full data without any missing for all outcomes. However, in case of missing data, two imputation methods, i) last observation forward, ii) multiple imputation assuming missing at random, will be considered.

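### The gait endpoint rests on a film rating that the protocol does not mask to visit or viewing order, and the recorded 30 m walk time belongs to no named endpoint

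*Protocol*

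**What the plan says.** The design is open label with one treated group of 20: "This is an open label, single center, pilot study of 20 participants with MPS".

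Section 9.1, secondary endpoint 4, defines the endpoint as "Gait: Qualitative assessment by physical therapist (i.e. improved, no change, worsened". Section 12.2 (secondary objective) carries the same three levels forward as the analysis variable: "Gait analysis results (improved, no change, worsened".

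Section 10.15 describes the procedure. The child is filmed from three directions over 30 m, and "total time to complete the 30 meters will be recorded". On the rating it says only: "These films will be viewed and rated by a certified pediatric physical therapist". The films are kept indefinitely.

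The stair test is built in a similar way (Section 10.17: "A 1-flight stair climb will be filmed and evaluated for ease of climb/descent"), but its endpoint keeps the time: "Stair climb/descent: Time and quality of movement".

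The schedule of events places gait and stair climb at Week -8, Day +1 and Week +36 only. Section 12.2 also promises descriptive statistics on all data collected, which would include the walk time.

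**The concern.** The MDRI components, the individual clinical response, the sleep diary and the stooling survey all come from caregivers, who also give the injections. They cannot be masked. The filmed tests differ because a film can be shown to a rater without its date. The protocol does not provide for this.

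A rating of improved or worse compares two visits. If it is assigned directly to films in known order, the rater also knows which film was taken on treatment, and any expectation about the drug can enter the label. Masking the rater is part of how the endpoint is measured, so it belongs in the protocol and is not a detail of analysis.

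The second point concerns the measure itself. The trial collects a continuous gait measure and then defines the endpoint without it. A three-level label carries less information than the number beside it, and the protocol gives no reason for treating gait differently from stairs.

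**Working it through.** **1. Passages side by side.** The protocol states no power or precision figure for gait, so there is none to reproduce.

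| Item | Gait | Stair climb |
|---|---|---|
| Filmed | yes (10.15) | yes (10.17) |
| Time recorded | yes, 30 m | yes, climb and descent |
| Time in the endpoint (9.1, 12.2) | no | yes |
| Qualitative rating in the endpoint | yes, three levels | yes |
| Masking of visit or viewing order | not stated | not stated |

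**2. What random, masked order achieves.** Suppose there is no true change between two films. Let s be the chance that the rater prefers the film seen second and f the chance that the rater prefers the film seen first. With random order, P(improved) = (s + f)/2 and P(worse) = (s + f)/2. The expected net improvement is zero whatever the rater's leaning. With known order that cancellation is lost.

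**3. Illustration of rating bias.** Assumptions, none from the documents: 20 ratable pairs, no true change, and an exact two-sided sign test of improved against worse at 0.05. The protocol does not name this test for gait. The rejection rate is the multinomial probability summed over all counts (improved, worse) for which the binomial p-value is below 0.05.

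| Improved / worse | Children out of 20 | Rejection rate |
|---|---|---|
| 20% / 20% (no leaning) | 4 / 4 | 1.9% |
| 30% / 20% | 6 / 4 | 5.0% |
| 40% / 20% | 8 / 4 | 13.2% |
| 40% / 10% | 8 / 2 | 36.7% |

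Row 2 moves 2 children from unchanged to improved and row 3 moves 4. Row 4 moves the equivalent of 2 from unchanged and 2 from worse.

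**4. Illustration of information lost.** Assumptions: 20 children, normally distributed change, three levels cut at ±0.5 SD of change, two-sided 0.05. For a true mean change d in SD units, P(improved) = Φ(d − 0.5) and P(worse) = Φ(−0.5 − d).

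| d | P(improved) | P(worse) | Power, paired t on the continuous value | Power, sign test on the three levels |
|---|---|---|---|---|
| 0.50 | 0.50 | 0.16 | 56% | 37% |
| 0.65 | 0.56 | 0.13 | 78% | 60% |
| 0.80 | 0.62 | 0.10 | 92% | 79% |

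**5. Link to the protocol's precision statement.** Section 12.3 gives a margin of about half an SD for paired continuous outcomes. The check is t(0.975, 19)/√20 = 2.093/4.472 = 0.468 SD, which agrees. That margin could describe walk time in 20 children. It cannot describe a three-level label.

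**6. What the visit schedule offers.** Taking the Day +1 film as baseline, each child has an off-drug pair (Week -8 to Day +1, 8 weeks) and a treatment pair (Day +1 to Week +36, 36 weeks). There is no Week +8 film. The intervals differ, so the off-drug pair is a partial control and not a matched one.

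**The case against.** Several stronger readings are tempting, and the documents do not support them.

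- *The rater knows which film was on drug.* A reader might infer this from the wording of the categories. Section 10.15 is silent on labelling, order and timing, and unlabelled films can be compared and classified afterwards. What can be said is that masking is not specified.
- *A single therapist rates everything.* This would rest on an indefinite article. The protocol does not fix the number of raters, and the point does not depend on it.
- *Gait is the trial's only source of objective efficacy evidence.* Stair-climb time is already a secondary endpoint, and the stool microbiome is a laboratory-measured exploratory one.
- *The walk time is thrown away.* Section 12.2 would summarise it descriptively. What it lacks is a place in a named endpoint.
- *Nothing controls for rater leaning.* A general tendency to call later films better would also show between Week -8 and Day +1. Only expectation tied to the drug escapes that comparison.

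A further objection has real force: walk time is not plainly the better measure here. These children may be hyperactive and need prompting, and the study hypothesis is that hyperactivity falls, so a slower walk could accompany benefit. Section 10.5 also allows for children who cannot stand, so some may not complete 30 m. This argues for keeping the therapist's rating and adding time beside it. It does not argue for leaving the time out, because stair time shares these limits and is used.

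Finally, gait is one of seven secondary endpoints in a pilot sized by feasibility. It does not enter the MDRI or the dose-escalation rule, and Section 12.2 already says that unadjusted secondary results will be read with caution. That limits the weight of the point but does not remove it.

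**Conclusion.** The point holds in a limited form. The protocol defines gait solely by a therapist's three-level rating of films, does not mask that rating in an open-label trial, and leaves a recorded continuous gait measure outside every named endpoint. A better procedure is available from material already collected.

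The consequence is that a gait result favouring treatment could not be separated from rater expectation, and a modest real change would be harder to detect. The documents give no rate of misrating. The rejection rates of 5% to 37% and the power differences of 13 to 19 percentage points (92% − 79% and 56% − 37%) follow from assumed shifts, cut-offs and effects, a test the protocol does not name for gait, and 20 children able to walk the distance. They show direction and plausible scale only. The point concerns how one secondary endpoint can be interpreted. It is worth correcting, but the safety and dose-escalation conclusions do not depend on it.

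**What to change.** - **Section 10.15, and the quality rating in Section 10.17:** have the therapist rate each child's stored Week -8, Day +1 and Week +36 films after the last one is made, with visit labels and dates removed and in random order. Derive improved, unchanged or worse after unmasking. Report the off-drug pair (Week -8 against Day +1) beside the treatment pair (Day +1 against Week +36), noting the unequal intervals.
- **Section 9.1, secondary endpoint 4, and Section 12.2:** add paired change in 30 m walk time as a supportive quantitative gait measure beside the rating, among children able to complete the walk. State that time may also reflect cooperation or hyperactivity.

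**Cost:** no new visit, test or staff, since the films are stored indefinitely and the time is already recorded. Files must be relabelled, ratings wait until the Week +36 film, and visible growth over the 44 weeks from first to last film (8 + 36) may partly reveal the order. Partial masking is still better than none.
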